## Abstract

Stopping smoking is crucial for public health and especially for individuals with diabetes. Combustion-free nicotine alternatives like e-cigarettes and heated tobacco products are increasingly being used as substitutes for conventional cigarettes, contributing to the decline in smoking prevalence. However, there is limited information about the long-term health impact of those products in patients with diabetes. This randomized controlled trial aims to investigate whether switching from conventional cigarettes to combustion-free nicotine alternatives will lead to a measurable improvement in cardiovascular risk factors and metabolic parameters over a period of 2 years in smokers with type 2 diabetes. The multicenter study will be conducted in seven sites across four countries. A total of 576 smokers with type 2 diabetes will be randomly assigned (1:2 ratio) to either standard of care with brief cessation advice (Control Arm) or combustion-free nicotine alternatives use (Intervention Arm). The primary end point is the change in the proportion of patients with metabolic syndrome between baseline and the 2-year follow-up. Additionally, the study will analyze the absolute change in the sum of the individual factors of metabolic syndrome at each study time point. Patient recruitment has started in September 2021 and enrollment is expected to be completed by December 2023. Results will be reported in 2026. This study may provide valuable insights into cardiovascular and metabolic health benefits or risks associated with using combustion-free nicotine alternatives for individuals with type 2 diabetes who are seeking alternatives to tobacco cigarette smoking. The study protocol, informed consent forms, and relevant documents were approved by seven ethical review boards. Study results will be disseminated through articles published in high-quality, peer-reviewed journals and presentations at conferences.

## Introduction

Diabetes is a major public health problem and its burden is increasing globally [1]. People with diabetes have increased health risks mainly secondary to the development of macrovascular (coronary artery disease, stroke, and peripheral arterial disease) and microvascular complications (nephropathy, retinopathy, and diabetic neuropathy) [2]. Cardiovascular complications are the most common, often being the cause of death [3].

In addition to diabetes and hyperglycemia, well-established cardiovascular risk factors encompass obesity, hypertension, dyslipidemia, and other factors falling under the umbrella of metabolic syndrome (MetS). Lifestyle plays a critical role in the determination of cardiovascular risk in people with diabetes, independently from factors reflecting MetS and diabetes severity. In this context, the coexistence of cigarette smoking is of particular relevance.

People with diabetes who smoke cigarettes are at increased risk of cardiovascular events and premature death and avoiding smoking can reduce this risk [3–5]. Given that exposure to cigarette smoke is associated with vascular damage, endothelial dysfunction, and activation of coagulation and fibrinolysis [6–8], it is not surprising that smoking exacerbates the detrimental effects of elevated blood glucose and other risk factors, accelerating vascular damage in people with diabetes.

While reducing exposure to cigarette smoke is important for public health, it becomes even more significant for people with Type 2 diabetes mellitus (T2D). Prevalence of cigarette consumption has significantly decreased, but this trend has not been observed in those with diabetes [9–11], justifying an urgent need to target this vulnerable population with effective smoking cessation interventions, including counseling and nicotine-containing preparations [5, 12–15].

Despite high-quality evidence supporting the efficacy of combining smoking cessation medications with counseling [12–15], the evidence for efficacious smoking cessation interventions in people with diabetes is limited [5, 16, 17]. Consequently, novel, and more efficient approaches are required.

Although not authorized as medications for smoking cessation, combustion-free technologies for nicotine delivery, such as e-cigarettes (ECs) and heated tobacco products (HTPs), have become de facto harm reduction tools from cigarette smoke [18–20] and aids for quitting smoking [21, 22]. Currently, there is insufficient evidence to recommend use of ECs or HTPs as a tobacco cigarette substitute among people with diabetes who smoke, and there are no long-term studies assessing cardiovascular risk or the impact on metabolic parameters in people with diabetes who use these technologies.

The DiaSmokeFree investigators aim to determine whether smokers with T2D who switch to combustion-free nicotine alternatives (C-F NA) experience measurable improvements in their cardiovascular risk factors and metabolic parameters. The protocol of this prospective, randomized, controlled trial is designed to provide valuable insights into the potential benefits or risks associated with using C-F NA for individuals with T2D who are seeking alternatives to tobacco cigarette smoking, particularly in relation to their cardiovascular and metabolic health.

## Methods

The study is designed to assess the impact of combustion-free nicotine alternatives (C-F NA) on cardiovascular risk factors and metabolic homeostasis as a consequence of avoiding individual exposure to cigarette smoke toxicants in smokers with T2D. It is a 24-month prospective international, multicenter, open-label, randomized, controlled, two parallel-arm study conducted in seven locations across four different countries.

## Study population

Participants will be recruited on a voluntary basis from a group of cigarette smokers who have been clinically diagnosed with T2D. Only patients who smoked daily for at least 5 years will be considered for inclusion in the study. To confirm the smoking status of potential participants, an exhaled carbon monoxide (eCO) measurement will be taken at the screening visit. The cutoff for confirmation as a smoker will be an exhaled CO level greater than or equal to 7 parts per million (ppm). To avoid including patients with poorly controlled diabetes requiring immediate modification of therapy, it was decided to set a glycated hemoglobin percentage of between 6 and 12% as an inclusion criterion. Another criterion is a BMI between 17.6 kg/m^2^ and 34.5 kg/m^2^ to achieve greater homogeneity of the group and to avoid subjects with morbid obesity and coexisting other metabolic disorders, which could affect the outcome of the study. Each participant identified as a smoker with T2D will be offered access to free smoking cessation programs aimed at helping participants quit smoking. Only those who refuse to participate in the smoking cessation programs and express willingness to switch to C-F NA will be eligible for randomization. Before randomization, participants will provide informed consent.

Participants will be required to satisfy all of the following criteria.

Inclusion criteria:Men or women diagnosed with T2D (as defined by the American Diabetes Association).Cigarette smokers of ≥ 10 cigarettes/day (max 30 cigarettes/day).History of regular smoking for at least 5 consecutive years.Verified smoking status (eCO ≥ 7 ppm).Willingness to switch to a C-F NA.Refusal to participate in smoking cessation programs.Glycated hemoglobin between 6 and 12%.Body mass index between 17.6 kg/m^2^ and 34.5 kg/m^2^, both inclusive.Body weight exceeding at least 50 kg (men) or 40 kg (women).

Exclusion criteria:History of recent (i.e., within 4 weeks prior to visit 1) acute decompensation of T2D requiring change of treatment.Known clinically significant cardiovascular, metabolic, respiratory, renal, psychiatric, or other major disorder that, in the opinion of the principal investigator, would jeopardize the safety of the participant or impact on the validity of the study results.Any other condition or therapy that would make the patient unsuitable for the studies and will not allow participation for the full planned study period (e.g., active malignancy or other condition limiting life expectancy to < 12 months).Desire to quit smoking within the next 6 months.A significant history of alcohol or drug abuse within 24 months prior to screening.Regular use of any nicotine (e.g., e-cigarettes, NRT, nicotine pouches) or tobacco product (e.g., heated tobacco products—HTPs, oral smokeless) other than their own cigarettes within 14 days of screening.Pregnant or breast-feeding or intention to become pregnant during the study.Active participation in another clinical trial.

### Study design

The study follows a randomized controlled design with two parallel groups: control (A) and intervention (B) (Fig. 1). The study will be conducted in seven locations across four different countries (UK, Italy, Poland, and Moldova). The setting for the study will be an ambulatory (outpatient) setting. The design of the trial follows the rules set by the Standard Protocol Items: Recommendations for Interventional Trials (SPIRIT) guidelines (SPIRIT checklist).

**Fig. 1 Fig1:**
[figure not shown]
Study design flow of DiaSmokeFree; *V* visit, *C-F NA* combustion-free nicotine alternatives

Participants will attend a screening visit within 28 days prior to study visit 1 (Tables 1 and 2). During the screening visit, socio-demographic data, detailed medical history (including medication use), and detailed history of smoking, vaping, and heated tobacco products (HTPs) use will be collected. Additionally, participants’ intention to quit smoking will be assessed. All patients will be offered a smoking cessation program according to the local guidelines. A second opportunity to enroll in a free smoking cessation program will be offered before study enrollment. Any participant who expresses the intention of booking for the cessation program or to quit smoking in the next 6 months will be urged to do so and not be recruited in the study. Patients taking part in the study will be informed that they are free to quit smoking and withdraw from the study at any time. Moreover, participants will be encouraged to quit smoking at every contact time point throughout the whole study.

**Table 1 Tab1:** Study assessments (Control group—Arm A)

Procedure	Screen (V0)	Baseline (V1) day 1	Week 12 (V2) day 90 ± 5	Week 24 (V3) day 180 ± 7	Week 52 (V4) day 360 ± 7	Week1 04 (V5) day 720 ± 7
Eligibility criteria check	X	X				
Medical Hx	X					
Medication use		X	X	X	X	X
Smoking/vaping Hx	X					
Cigarette consumption	X	X	X	X	X	X
Exhaled CO		X	X	X	X	X
FTND		X				
Intention to quit	X	X				
Informed consent		X				
Randomization		X				
Tracker APP installation		X				
Vital signs		X	X	X	X	X
Weight, BMI, waist circumference		X	X	X	X	X
Body composition equation*		X	X	X	X	X
QoL questionnaire		X	X	X	X	X
Smoking cessation advice	X	X	X	X	X	X
Spirometry		X				X
Metabolic syndrome assessment**		X	X	X	X	X
Blood sample***		X	X	X	X	X
Testosterone (men only)		X	X	X	X	X
Urine albumin to creatinine ratio (ACR)						
Safety reporting		X	X	X	X	X

*BL* baseline, *V* visit, *Hx* history, *CO* carbon monoxide, *BMI* body mass index, *FTND* Fagerstrom Test for Nicotine Dependence, *QoL* quality of life, *CBC* complete blood count, *WBC* white blood cells, *Hb* hemoglobin, *LDL* low-density lipoprotein, *HDL* high-density lipoprotein, *HbA1*_*C*_ glycated hemoglobin, *AE/SAE* (serious) adverse incidents

*Body composition (fat and skeletal muscle mass) by validated equation by Lean ME et al. (1996) and Al-Gindan YY et al. (2014)

**Metabolic syndrome is defined according to the National Cholesterol Education Program (NCEP) criteria as having ≥ 3 of the following five features:

1—fasting plasma glucose ≥ 6.1 mmol/L (110 mg/dL)

2—blood pressure ≥ 130/ ≥ 85 mmHg or treatment for hypertension

3—triglycerides ≥ 1.69 mmol/L (150 mg/dL) or treatment for high triglycerides

4—high-density lipoprotein (HDL) cholesterol < 1.29 mmol/L (50 mg/dL) for females or < 1.04 mmol/L (40 mg/dL) for males or treatment for low HDL

5—waist circumference ≥ 88 cm (35 in) for females or ≥ 102 cm (40 in) for males

***To measure: CBC (WBC Hb, platelets), lipid profile (triglycerides, LDL and HDL cholesterol) HbA1_c_, insulin level

**Table 2 Tab2:** Study assessments (intervention group—Arm B)

Procedure	Screen (V0)	BL (V1)	Wk2	Wk4	Wk8	Wk12 (V2)	Wk20	Wk24 (V3)	Wk32	Wk40	Wk48	Wk52 (V4)	Wk60	Wk68	Wk76	Wk84	Wk92	Wk100	Wk104 (V5)
Eligibility criteria check	X	X																	
Medical Hx	X																		
Medication use		X				X		X				X							X
Smoking/vaping Hx	X																		
Cigarette consumption	X	X	X	X	X	X	X	X	X	X	X	X	X	X	X	X	X	X	X
Exhaled CO		X	X	X	X	X	X	X	X	X	X	X	X	X	X	X	X	X	X
FTND		X																	
C-F NA use			X	X	X	X	X	X	X	X	X	X	X	X	X	X	X	X	X
Intention to quit	X	X																	
Informed consent		X																	
Randomization		X																	
Tracker APP installation		X																	
C-F NA familiarization		X																	
Vital signs		X				X		X				X							X
Weight, BMI, waist circumference		X				X		X				X							X
Body composition equation*		X				X		X				X							X
QoL questionnaire		X				X		X				X							X
Smoking cessation advice	X	X	X	X	X	X	X	X	X	X	X	X	X	X	X	X	X	X	X
Spirometry		X																	X
Metabolic syndrome assessment**		X				X		X				X							X
Blood samples***		X				X		X				X							X
Urine albumin to creatinine ratio (ACR)		X				X		X				X							X
Testosterone (men only)		X				X		X				X							X
Safety reporting		X				X		X				X							X
Provide C-F NA device (+ 2 wks supply of consumables)		X																	
Hand out 2 wks supply of consumables			X																
Hand out 4 wks supply of consumables				X	X		X				X							X	
Hand out 2 × 4 wks supply of consumables						X		X	X	X		X	X	X	X	X	X		
Product use checks (collect used and unused consumables)			X	X	X	X	X	X	X	X	X	X	X	X	X	X	X	X	X

*BL* baseline, *V* visit, Hx history, *CO* carbon monoxide, *BMI* body mass index, *FTND* Fagerstrom Test for Nicotine Dependence, *QoL* quality of life, *CBC* complete blood count, *WBC* white blood cells, *Hb* hemoglobin, *LDL* low-density lipoprotein, *HDL* high-density lipoprotein, *HbA1*_*C*_ glycated hemoglobin, *AE/SAE* (serious) adverse incidents, *C-F NA* combustion-free nicotine alternatives

*Body composition (fat and skeletal muscle mass) by validated equation by Lean ME et al. (1996) and Al-Gindan YY et al. (2014)

**Metabolic syndrome is defined according to the National Cholesterol Education Program (NCEP) criteria as having ≥ 3 of the following five features:

1—fasting plasma glucose ≥ 6.1 mmol/L (110 mg/dL)

2—blood pressure ≥ 130/ ≥ 85 mmHg or treatment for hypertension

3—triglycerides ≥ 1.69 mmol/L (150 mg/dL) or treatment for high triglycerides

4—high-density lipoprotein (HDL) cholesterol < 1.29 mmol/L (50 mg/dL) for females or < 1.04 mmol/L (40 mg/dL) for males or treatment for low HDL

5—waist circumference ≥ 88 cm (35 in) for females or ≥ 102 cm (40 in) for males

***To measure: CBC (WBC Hb, platelets), lipid profile (Triglycerides, LDL and HDL cholesterol) HbA1_c_, insulin level

On day 1, baseline assessments will be performed for all participants (Tables 1 and 2). This includes measurements and evaluations related to cardiovascular risk factors, metabolic homeostasis, and general health. Following the baseline assessments, participants will be randomly assigned to either the control (A) arm or the intervention (B) arm. The randomization sequence will be computer generated, with an allocation ratio of 1:2 (arm A:arm B) to account for the estimated 50% proportion of subjects achieving sustained reduction in cigarette consumption of at least 80% in the arm B (see “Statistical Considerations”).

Participants randomized into the intervention arm (B) will be allowed to choose a preferred C-F NA (e-cigarettes, HTPs, etc.) from a given pool of popular options present in the respective markets. They will receive training and counseling on how to use the chosen device and will be provided with a full 2-week supply of the required consumables (cartridges/pods or e-liquids refill bottles for e-cigarettes, tobacco sticks for HTPs) on day 1. Participants randomized into the control arm (A) will be offered the usual standard of care, which includes brief smoking cessation counseling at each visit.

After randomization, participants’ smartphones will be equipped with a dedicated tracker application. This application is designed to monitor individual behaviors such as physical activity, adherence to capillary blood glucose monitoring, cigarette smoking frequency and daily C-F NA usage. The tracker application will also identify any protocol violations, collect adverse events and send reminders (e.g., next scheduled appointment, study restrictions, instructions) throughout the study duration. The use of a dedicated tracker application adds an innovative element to continuously collect data and enhances adherence to the study protocol.

After the baseline assessments (Visit 1), participants will be invited to attend four more clinical visits (Visits 2–5), which will be conducted in an ambulatory (outpatient) setting. During these visits, a number of measurements will be taken, with a particular focus on metabolic syndrome parameters, i.e., waist circumference, systolic blood pressure value, venous blood concentration of triglycerides, HDL, and fasting blood glucose (Tables 1 and 2). Also, two questionnaires will be used.

(Diabetes Quality of Life questionnaire and the Fagerström Test for Nicotine Dependence) to assess specific aspects of participants' health and smoking behavior.

Following each clinical visit, participants will be provided with an appropriate number of consumables (cartridges/pods or e-liquids refill bottles for e-cigarettes, tobacco sticks for HTPs) if they are in the intervention arm (Arm B). Participants in the intervention arm will have additional non-clinical visits between the clinical visits. These non-clinical visits are designed to replace any used consumables and provide an opportunity for study investigators to stimulate retention and check compliance. At these non-clinical visits, participants in Arm B will be required to return all empty, part-used, and unused consumables from the previous study period. This evaluation of the habitual pattern of C-F NA use and verification of product adherence are essential for monitoring the participants' compliance with the intervention.

Before each study visit, participants will be required to fast overnight (from midnight). During the clinic visits, clinical laboratory evaluations will be performed on fasting blood samples. Participants will also receive instructions to refrain from consuming alcohol for 24 h prior to clinic visits and will be advised not to consume more than 14 units of alcohol per week throughout the entire study duration. This is to minimize any potential interference of alcohol consumption with study outcomes and to maintain consistency in data collection. Throughout the study, any modifications in participants' diet and/or anti-diabetic medication will be regularly recorded and monitored.

At each visit, all participants will be advised and encouraged to completely quit smoking. They will be explicitly informed about the risks associated with smoking and will be offered referral to free smoking cessation programs at every contact time point.

Premature withdrawal from the study may occur if a participant experiences a severe adverse event (SAE), sustains any uncorrectable protocol deviations during the study, exhibits uncooperative behavior or non-attendance, decides to stop their participation at any time, becomes pregnant, or decides to accept the investigators advice to completely stop smoking.

The DiaSmokeFree study is designed as an unblinded trial due to the nature of the intervention, where participants and trial staff cannot be blinded to the specific intervention being provided (either C-F NA or brief smoking cessation counseling).

To ensure the integrity and reliability of the study data, the source data and source documents will be managed according to Good Clinical Practice (GCP) guidelines. The trial will formally conclude on the date of the last visit of the last patient in the last country participating in the trial.

For data collection, each individual patient will be allocated an electronic case report form (eCRF). Anonymized data from each study visit will be entered directly onto the eCRF, which will then serve as a source document for the trial. This data entry process ensures that data is collected accurately and consistently at all study sites. To maintain data quality, the study will use standardized instruments, such as the Diabetes Quality of Life questionnaire and the Fagerström Test for Nicotine Dependence, to assess specific aspects of participants' health and smoking behavior.

To protect participants’ privacy and confidentiality, each participant will be assigned a unique study identification number (patient ID). Participants' personal data will not be linked to the research results, and only a limited number of members of the research team will have access to the decoding list that links participant IDs to their personal information. All information obtained during the study procedures, including participant data and personal details, will be treated as private and confidential, in accordance with ethical and privacy regulations.

Compliance will be checked by counting all empty, partially used and unused consumables returned at each visit (i.e., consumables record checks) and by reviewing any non-compliance recorded in the research diary or via the tracker app.

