### Objectives and end points

Primary end points: The primary objective of the study is to assess the impact of sustained use of C-F NA on the proportion of patients with metabolic syndrome (MetS) among individuals with T2D. The MetS will be defined by the National Cholesterol Education Program (NCEP) MetS score [23], and the primary end point will be the change in the prevalence of an NCEP MetS score below the diagnostic threshold (< 3) between baseline and the 2-year follow-up. The comparison will be made between patients with T2D in both arms of the study.

Secondary end points: The study will also assess the change in MetS prevalence at 3 months, 6 months, and 1 year as secondary outcomes. All assessments at each time point will be performed in all participants in both arms of the study.

Considering the results of several lifestyle modification interventions, the absolute reduction in MetS prevalence after smoking cessation is expected to be no less than 15% [24–28].

Additionally, the study will analyze the absolute change in the sum of the individual factors of MetS, as defined by NCEP criteria, at each study time point (between and within study groups. Other secondary end points will include changes in each individual factor of MetS and changes in the variables at each study time point (between and within study groups).

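### The two assessment schedules disagree on urine ACR: no visit is marked for the control arm, while five are marked for the intervention arm

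*Protocol article*

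**What the plan says.** The protocol article gives each arm its own schedule in the Study design section. Table 1 is headed "Study assessments (Control group—Arm A") and Table 2 "Study assessments (intervention group—Arm B"). Both contain the row "Urine albumin to creatinine ratio (ACR"). In Table 1 the row has no mark in any of its six columns (V0 to V5). In Table 2 it is marked at baseline (V1) and at weeks 12, 24, 52 and 104 (V2 to V5).

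The text after Table 2 states: "On day 1, baseline assessments will be performed for all participants (Tables 1 and 2"). It continues: "Following the baseline assessments, participants will be randomly assigned to either the control (A) arm or the intervention (B) arm".

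Objectives and end points states: "All assessments at each time point will be performed in all participants in both arms of the study". It then adds: "Other secondary end points will include changes in each individual factor of MetS and changes in the variables at each study time point", both between and within the study groups.

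**The concern.** A schedule of assessments is operative text, because it tells a site what to collect and when. As printed, the two schedules would have ACR collected in one randomized arm and not in the other, although both arms attend the same five clinical visits.

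What is at stake is the between-arm reading of this one variable. With follow-up values in Arm B only, a change over 24 months could not be separated from the course of the diabetes, from changes in medication or from regression to the mean. ACR is the only urine or renal measure in either schedule, and the Introduction lists nephropathy among the microvascular complications of diabetes. No other row would supply the information for controls.

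**Working it through.** No sample-size or power figure decides this point. The check is a comparison of the two rows, followed by a count.

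**1. The ACR rows side by side**

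| | V1 | V2 | V3 | V4 | V5 | Marked |
|---|---|---|---|---|---|---|
| Table 1 (Arm A) | – | – | – | – | – | 0 of 5 |
| Table 2 (Arm B) | X | X | X | X | X | 5 of 5 |
| Marked in both | no | no | no | no | no | 0 of 5 |

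**2. Could another Arm A row cover ACR?** The footnote to the blood-sample row lists "CBC (WBC Hb, platelets), lipid profile (triglycerides, LDL and HDL cholesterol"), plus HbA1c and insulin. It contains no urine measure, so the answer is no.

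**3. Is the whole of Table 1 damaged?** It does not appear so. The neighbouring rows for blood sample, testosterone and safety reporting each carry their marks at V1 to V5, as they do in Table 2. Only the ACR row is blank throughout.

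**4. Can the V1 cells be carried out as printed?** They cannot. Baseline assessments come before randomization, so a site does not know the arm when V1 measurements are made. A V1 sample intended for Arm B alone would have to be taken from everyone or delayed until after allocation, and the second course departs from the stated order. The conflict at V1 therefore exists without any help from Objectives and end points. It also means that the tables cannot show whether a control baseline exists.

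**5. Size**

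The plan's own total comes first. The sample-size section requires 160 controls and 320 intervention participants with analyzable data, each increased by 20%:

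- Control: 160 × 1.2 = 192
- Intervention: 320 × 1.2 = 384
- Total: 192 + 384 = 576, which matches the stated total and the 1:2 ratio

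ACR measurements scheduled after baseline (V2 to V5, four visits):

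- Arm B, as printed in Table 2: up to 384 × 4 = 1,536
- Arm A, as printed in Table 1: 192 × 0 = 0
- Arm A, if the row were filled in: up to 192 × 4 = 768

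The figure of 768 is an upper limit with no dropout. If the expected 20% withdrawal all happened before V2, it would be 192 × 0.8 × 4 = 614.4, or about 614. The control follow-up measurements in doubt therefore lie between about 614 and 768. The 192 possible control values at V1 are left out of this count for the reason in step 4.

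**The case against.** The strongest reply is that this is an unfinished table row and not a decision to leave controls unmeasured. Rows that do not apply to Arm A, such as those on use and supply of the combustion-free products, are absent from Table 1 altogether, whereas ACR is listed. The ACR and testosterone rows also stand in opposite order in the two tables, which suggests an editing slip. A fault in typesetting or text extraction cannot be ruled out either. This largely stands: an omission is the likeliest explanation. It does not remove the contradiction, and it does not show which version sites follow.

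A second reply is that the sentence promising all assessments in both arms directly follows the one on MetS prevalence at 3 months, 6 months and 1 year, and may refer only to those assessments. That narrower reading is possible. The conflict with that section then rests only on the general phrase about changes in the variables. The conflict with the baseline text remains.

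A third reply is that the article condenses a fuller protocol, and that recruitment began in September 2021 under documents approved by seven ethics committees. Nothing shows that sites work from the article's Table 1. This is correct, and it limits what can be claimed about data collected so far.

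A reader might infer that the trial will have no control ACR data, that all five visits (192 × 5 = 960 samples) are lost, and that the baseline cannot be recovered. The documents do not support this. V1 precedes allocation, so a baseline for one arm only cannot be carried out as printed, and control baselines may well exist. The blank row shows what the article schedules and is no evidence of what sites have done.

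**Conclusion.** The inconsistency is real. Table 1 and Table 2 conflict on ACR, and both cannot be squared with baseline assessments done in all participants before randomization. On its broad reading, the statement in Objectives and end points conflicts with Table 1 as well. If Table 1 is followed as printed, none of the four follow-up visits allows a between-arm comparison. The baseline status of controls is unknown.

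The consequence is limited. ACR is not named as an end point and enters only through the general reference to changes in the variables. The primary MetS end point, its power, the sample size and the named secondary end points are untouched. This is a reporting inconsistency that should be corrected and checked with sites, and not a flaw in the design.

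The conclusion assumes that the extracted Table 1 reflects the published one, which the intact neighbouring rows make likely. The loss of follow-up comparisons depends further on sites acting on that table.

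**What to change.** 1. Reconcile Table 1 with Table 2, with the baseline text and with Objectives and end points by marking ACR at V1 to V5 for Arm A. Check that the full protocol, the site schedules and the eCRF agree.
2. Ask each site now whether ACR has been taken in control participants, and at which visits, V1 included.
3. If some control values are missing, compare the arms only at visits where both were measured. Use change from baseline only where V1 was measured in both arms, and otherwise compare follow-up values. State the number measured by arm and visit.
4. Do not interpret a change seen in Arm B alone as an effect of the intervention.

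The cost is a corrected table row, one query to seven sites and, where sampling has been missed, a urine sample from controls at clinical visits that they already attend. The sample size and the primary analysis do not change. A delay costs more, because a follow-up sample that was not taken at its visit cannot be obtained afterwards.
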